# 8. STATISTICAL CONSIDERATIONS

### 8.1. SAMPLE SIZE OR POWER CALCULATION

**Study 1**

A sample size of 403 participants will be needed to detect a meaningful change in dementia risk scores (-0.3 Z score, SD = 0.5) between baseline and three-month follow-up (with 90% power and α=0.05), and a drop out rate of 25%.

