**Statistical considerations**

**Sample size calculation**

Study 1 500 older adults are required to detect a meaningful change in dementia risk scores at two time points

Study 2 40 older adults will be suitable to sufficiently address the research question at hand and reach data saturation

Study 3 100 older adults and 100 adults will be recruited to determine sample size for this feasibility study

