### 8.2. PROVIDE A DETAILED ANALYSIS PLAN

**Study 1**

All surveys will be visually inspected for completeness on collection to minimise missing data. Assessment data will be entered into databases and analysed using standard statistical software (eg. SPSS V.22). Quantitative data obtained in response to structured assessment items will be entered, cleaned, analysed and summarised. The investigators will use descriptive statistics to describe the study group and to summarise their use of various components of the Brain Bootcamp Pack over the course of three months. Paired sample t tests will be used to analyse changes in our primary outcome, brain health risk profile, from baseline to three months. Nonparametric correlations will be conducted to examine the relationship between secondary outcomes (social networks, quality of life, motivation and dementia awareness) and changes in primary outcome.

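### The Study 1 sample size of 403 does not follow from its stated inputs, which give about 43 enrolled, and the Summary calls 500 required for the same purpose without linking the two

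*Protocol*

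**What the plan says.** Section 8.1 (Study 1) gives a sample size with its inputs: "A sample size of 403 participants will be needed to detect a meaningful change in dementia risk scores (-0.3 Z score, SD = 0.5". The comparison is "between baseline and three-month follow-up", "with 90% power and α=0.05", "and a drop out rate of 25" per cent. It does not say whether the SD of 0.5 belongs to the change or to the score at one visit, whether α is one- or two-sided, or whether 403 is counted before or after dropout.

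Section 8.2 (Study 1) names the test: "Paired sample t tests will be used to analyse changes in our primary outcome, brain health risk profile, from baseline to three months". Section 4.1 describes a single-group pre-post study.

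The Summary, under Sample size calculation, gives another number for the same purpose: "500 older adults are required to detect a meaningful change in dementia risk scores at two time points". The planned sample in the Summary and in Section 4.2 is also 500. Section 1.1 describes a government-funded campaign that will deliver 500 free boxes. Nothing in the protocol connects 403 with 500.

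**The concern.** A change of 0.3 against an SD of 0.5 is a standardised effect of 0.6, which a paired test detects with a few dozen people. A requirement of 403 is out of proportion to that. Either the number belongs to a different calculation, or the effect or SD was written down wrongly.

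Two things are at stake. First, the reader cannot tell what the study was sized to detect. Section 8.1 is also the only place where the protocol puts a number on a meaningful change in the risk score, so an error there touches the benchmark for the result. Second, taken at face value, 8.1 suggests a study just adequate for a change of 0.3. On the stated SD, the planned sample would find much smaller changes statistically significant.

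**Working it through.** **Inputs.** From Section 8.1: change 0.3 (absolute value), SD 0.5, power 90%, α = 0.05, dropout 25%. From Section 8.2: paired t test. Assumption: two-sided α, since sidedness is not stated.

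**Attempt to reproduce 403.** Take 0.5 as the SD of the change.

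- d = 0.3 / 0.5 = 0.6
- Normal approximation: n = ((1.960 + 1.282) / 0.6)² = 29.2, so 30 pairs
- Exact noncentral t: 32 pairs
- With dropout: 32 / (1 − 0.25) = 42.7, so 43 enrolled

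The stated figure is about nine times this (403 / 43 = 9.4).

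**Other readings of the SD.** If 0.5 is the SD at each visit, the SD of the change is 0.5 × √(2(1 − r)), where r is the pre-post correlation. The protocol gives no r, so a range is shown. The last two rows set the stated 0.5 aside and give the Z score an SD of 1 at each visit. All rows use 90% power and two-sided 0.05.

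| Reading | SD of change | Pairs | Enrolled (÷ 0.75) |
|---|---|---|---|
| 0.5 is the SD of change | 0.5 | 32 | 43 |
| 0.5 per visit, r = 0.5 | 0.5 | 32 | 43 |
| 0.5 per visit, r = 0 | 0.707 | 61 | 82 |
| 0.5 per visit, r = −1 (extreme) | 1.0 | 119 | 159 |
| SD 1 per visit, r = 0.5 | 1.0 | 119 | 159 |
| SD 1 per visit, r = 0 | 1.414 | 236 | 315 |

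**Other variants, with d = 0.6.**

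- One-sided α: 26 pairs, 35 enrolled
- 80% power: 24 pairs, 32 enrolled
- Bonferroni over 12 tests: 52 pairs, 70 enrolled
- Two independent groups, which is not the design: 120 in total, 160 with dropout

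None of these comes near 403.

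**Working back from 403.** If 403 is enrolled, 403 × 0.75 = 302 complete. With 302 pairs, 90% power is reached at d = 0.187. That is a change of 0.187 × 0.5 = 0.094 at the stated SD, or an SD of change of 0.3 / 0.187 = 1.60 at the stated change. Neither matches the text.

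**403 against 500.**

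- 403 as enrolled: 302 / 0.75 = 402.7, which rounds up to 403. Then 500 exceeds the calculated number.
- 403 as completers: 403 / 0.75 = 537.3, so 538 would be enrolled. The incorrect inflation 403 × 1.25 gives 504, close to 500 but not equal to it.

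**What the planned 500 delivers.**

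- Completers: 500 × 0.75 = 375 pairs
- 90% power, two-sided 0.05: d = 0.168, about 0.17 SD of the change score. At SD 0.5 this is 0.168 × 0.5 = 0.084.
- Smallest observed change with p < 0.05 at SD 0.5: 1.966 × 0.5 / √375 = 0.051, about one-sixth of 0.3

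**The case against.** The best defence is that the error is harmless. It runs towards too many participants, the 500 comes from a funded campaign, and neither the enrolment target nor the test would change. That stands, and it limits the point to the stated justification.

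Four stronger readings are tempting, and the protocol does not support them.

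- *The study is underpowered.* It is not. At d = 0.6, power with 302 completers is effectively 100%.
- *500 falls short of the requirement because 375 completers is below 403.* This takes 403 as completers. The dropout rate stands in the same sentence as 403, so enrolled is the more natural reading, and then nothing falls short. What remains is a wording conflict: two numbers are presented as needed for one purpose.
- *403 is the figure that is wrong, by a factor of nine.* The factor assumes that 0.5 is the SD of the change and that α is two-sided. The fault could equally lie in the 0.3 or the 0.5.
- *A significant p value will be presented as a meaningful change in risk score.* No passage says so. A gap between significance and relevance exists in any trial: with only 32 pairs, an observed change of about 0.18 would already be significant. The larger sample widens the gap, which is a reason to show the interval and not evidence of a planned misreading.

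**Conclusion.** The statement in Section 8.1 is wrong as written. Its inputs give 32 pairs and about 43 enrolled if 0.5 is the SD of the change and α is two-sided. If 0.5 is the per-visit SD, the requirement is 82 enrolled at zero correlation and cannot exceed 159. The finding that 403 is not reproducible does not depend on which reading is chosen. It follows that at least one of 403, 0.3 and 0.5 is misstated; the document does not show which.

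The Summary's description of 500 as required is a lesser fault of wording. Power is not threatened and no participant number needs to change. What fails is the stated basis for the sample size.

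**What to change.** In Section 8.1, state what the SD of 0.5 refers to, whether α is two-sided, and whether 403 is before or after dropout. Then correct whichever of N, effect or SD is wrong. Only the sponsor can say which, so the correction should start from the original calculation and should not be fitted to 403 afterwards.

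In the Summary, describe 500 as the planned campaign enrolment, not as a statistical requirement. Add what it delivers, labelled as following from a fixed enrolment: with 25% dropout, 375 pairs, and 90% power (two-sided 0.05) for a mean change of about 0.17 SD of the change score.

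In Section 8.2, say that the mean change will be reported with its 95% CI beside the stated meaningful change of 0.3. This is a matter of presentation; no new success criterion based on the interval is needed.

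The cost is a few sentences in 8.1, 8.2 and the Summary. Enrolment, data collection and the planned test stay as they are.

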**Study 2**

A theoretical sampling approach will be used to select participants based on their analytical relevance to the study question, in order to achieve the experience of individuals with different dementia risk profiles and those who dropped out of the study. Sampling will end once saturation has been reached (i.e., no new themes are emerging, and the research findings are coherent and explicable). We estimate that this will involve a sample size of 40 participants.

**Study 2**

Based on a power analysis for biserial correlation using G*Power 3 with a conservative medium effect of ρ = .30 [47]report very high effect sizes with a similar design), and 80% power, an N of 64 is required to detect an association at p = .05 for each group. The final proposed sample size (N=100 per group) was larger than required for the present study to account for potential drop-outs between assessments.

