**Study 3**

Descriptive data will be compared between the groups using a two-sample t test and the Fisher exact test for continuous and categorical variables, respectively. Summary statistics will be calculated individually for the Virtual Reality Cognitive Screener, traditional cognitive assessment and questionnaire-dependent feedback scores. Younger and older adults (and older adults with cognitive impairment) cognitive performance on all measures will be compared using the two-sample t tests.

Performance scores will be analysed at each task level, given a total score, and compared between the older cognitive-intact and younger groups using the methods described above, as appropriate. Correlation between performance scores and other variables will assessed using Pearson correlation. A logistic regression will performed based on the total performance scores, followed by ROC analysis to assess its predictive capability to discriminate between cognitively intact and cognitively impaired individuals. Analyses will be performed using SPSS V22.0.

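### Study 3's required N of 64 per group holds only for a one-sided test that the protocol never declares; at two-sided 0.05 the requirement is 82 to 85

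*Protocol*

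**What the plan says.** Protocol Section 8.1 has two blocks headed Study 2. The first covers the 40 interviews. The second can only concern Study 3, because it refers to two groups of 100, which are the Study 3 numbers in the Summary and in Section 4.2.

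That second block gives the method ("Based on a power analysis for biserial correlation using G*Power 3"), the effect size ("with a conservative medium effect of ρ = .30") and 80% power, and concludes that "an N of 64 is required to detect an association at p = .05 for each group". It then explains the planned enrolment: "The final proposed sample size (N=100 per group) was larger than required for the present study to account for potential drop-outs between assessments". It gives no drop-out rate and does not say whether the test is one-sided or two-sided.

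Section 8.2, Study 3, names the matching analysis: "Correlation between performance scores and other variables will assessed using Pearson correlation". It states no direction and no one-sided test there, or for any other Study 3 comparison.

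**The concern.** The text speaks of a power to "detect an association at p = .05". An association without a direction, tested at 0.05, is ordinarily read as a two-sided test, and a Pearson correlation with no direction stated is ordinarily reported with a two-sided p-value. On that reading 64 is too small for the stated effect and power.

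Two statements depend on it. One is the claim of 80% power at 64 per group. The other is the justification of 100 per group as exceeding the requirement so as to absorb losses: the further the true requirement lies above 64, the smaller that allowance is.

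**Working it through.** **Inputs, all from Section 8.1 (second block headed Study 2):** ρ = 0.30; power 80%; α = 0.05; stated requirement 64 per group; planned 100 per group. Sidedness is not given, so both are computed.

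**1. Reproducing the stated figure (point-biserial model).** The test statistic is noncentral t with N − 2 degrees of freedom and noncentrality

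δ = √(ρ² / (1 − ρ²)) × √N = √(0.09 / 0.91) × √N = 0.3145 × √N.

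At N = 64, δ = 0.3145 × 8 = 2.516.

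- One-sided 0.05: critical t (62 df) = 1.670; power = 80.05%. At N = 63 power is 79.5%, so 64 is the smallest N that reaches 80%.
- Two-sided 0.05: critical t (62 df) = 1.999; power = 69.7%.

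The stated 64 is therefore exactly the one-sided answer.

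**2. Two-sided requirement, same model.**

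- N = 81: power 79.8%.
- N = 82: δ = 2.848, critical t (80 df) = 1.990, power 80.3%.

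The requirement is 82 per group.

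**3. Requirement for the planned Pearson correlation (Fisher's z).**

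N = ((z for α + z for power) / atanh ρ)² + 3, with atanh 0.30 = 0.3095.

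- Two-sided: ((1.960 + 0.842) / 0.3095)² + 3 = 84.9, so 85.
- One-sided: ((1.645 + 0.842) / 0.3095)² + 3 = 67.5, so 68.

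Power at N = 64, two-sided: Φ(√61 × 0.3095 − 1.960) = Φ(0.457) = 67.6%. A simulation of the Pearson test on bivariate normal data (100,000 samples) gave 68.3% at N = 64 and 80.3% at N = 85, in agreement.

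**4. What 100 per group provides at two-sided 0.05.**

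| Model | Required N | Power at 64 | Power at 100 | Loss that 100 can absorb |
|---|---|---|---|---|
| Point-biserial | 82 | 69.7% | 87.6% | 100 − 82 = 18 (18%) |
| Pearson, Fisher's z | 85 | 67.6% | 86.2% | 100 − 85 = 15 (15%) |

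Taken at face value, the protocol's 64 implies a margin of 100 − 64 = 36 (36%). The protocol does not print this percentage; it follows from its two numbers.

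**The case against.** The strongest reply is that 64 is not a miscalculation. It is exact for a one-sided test, no passage says that Study 3 is tested two-sided, and a direction is natural: hypothesis 4 in Section 2 expects the screener to separate intact from impaired participants, and agreement with the telephone test would be expected to be positive. This stands to the extent that a declared one-sided test would be defensible and would make the point-biserial figure correct. But the protocol does not declare one, and it fixes a required N that cannot be recovered from its stated inputs under the usual reading. Even one-sided, the planned Pearson correlation needs 68 by Fisher's z, not 64.

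A second reply is that the design hardly suffers, and this stands in full. A reader might infer that Study 3 is underpowered. At the planned 100 per group it is not, for the stated effect.

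A reader might also apply Study 1's 25% drop-out rate here and conclude that power falls below 80%. The documents do not support that: the Study 1 rate belongs to a three-month follow-up, whereas Section 6.6 places the two Study 3 assessments within a week of each other. No Study 3 rate is given, so whether 15 to 18% is enough cannot be judged.

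Finally, a reader might extend the point to the aim of separating impaired from intact participants, for which Section 8.2 says "A logistic regression will performed based on the total performance scores, followed by ROC analysis". How precise that would be depends on how many participants are impaired and how large the difference is. The protocol gives neither, so no figure for it follows from this calculation.

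**Conclusion.** The stated requirement is wrong on the ordinary two-sided reading and right only for a one-sided test that is declared nowhere. Two-sided, the requirement is 82 per group (point-biserial) or 85 (Pearson), against the stated 64. Power at 64 is about 68 to 70%, against the stated 80%. The drop-out allowance within 100 is about 15 to 18%, against an implied 36%.

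This rests on ρ = 0.30 and 80% power as stated, on reading an undirected association at 0.05 as two-sided, and on the point-biserial model as the source of 64, which the exact match supports. The consequence is limited to a misstated requirement and an overstated margin: enrolment of 100 per group needs no change, and power is about 86 to 88% if all complete.

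**What to change.** In Section 8.1, keep 100 per group and restate the basis: two-sided α = 0.05, 80% power, ρ = 0.30, 85 per group for the planned Pearson correlation (82 under the point-biserial model). Add that 100 per group allows about 15% loss (18% under the point-biserial model) and gives about 86 to 88% power with no loss. Name one model and use it throughout, so that the figure in 8.1 matches the test in 8.2.

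Alternatively, declare and justify a one-sided test in both 8.1 and 8.2. In that case 64 stands under the point-biserial model, and 68 applies for Pearson by Fisher's z.

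In either case, change the heading of this block from Study 2 to Study 3.

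The cost is a few sentences. Enrolment and procedures do not change. Under the two-sided restatement the declared drop-out margin is less favourable than the one now implied.

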### 8.2. PROVIDE A DETAILED ANALYSIS PLAN

**Study 1**

All surveys will be visually inspected for completeness on collection to minimise missing data. Assessment data will be entered into databases and analysed using standard statistical software (eg. SPSS V.22). Quantitative data obtained in response to structured assessment items will be entered, cleaned, analysed and summarised. The investigators will use descriptive statistics to describe the study group and to summarise their use of various components of the Brain Bootcamp Pack over the course of three months. Paired sample t tests will be used to analyse changes in our primary outcome, brain health risk profile, from baseline to three months. Nonparametric correlations will be conducted to examine the relationship between secondary outcomes (social networks, quality of life, motivation and dementia awareness) and changes in primary outcome.

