**Analysis plan**

Study 1 Descriptive analysis of baseline profile of participant demographics (age, gender, economic status) will be presented.

Non-parametric correlations and paired sample t-tests will be conducted to examine and analyse changes in primary outcome (dementia awareness, brain health risk profile) at baseline to three months.

**Study 2** Interview data will be analysed qualitatively for content and themes that emerge, and coded and categorised using N Vivo software

**Study 3** Descriptive statistics will be calculated for participant demographics and domains of the virtual reality screener and the traditional cognitive assessments. This will include percentage of participants who successfully completed the virtual reality cognitive assessments, time taken to complete the virtual reality cognitive assessment module, and scores from the feedback questionnaire.

Correlational analyses and receiver operating curve (ROC) will be conducted for performance scores on the virtual reality assessment module and scores on other cognitive assessment tests.

Duration of the Study 24 months

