### 6.4. PARTICIPANT ENROLMENT

**Study 1**

The participant will be enrolled into the study after the informed consent process has been completed. We request general public participants to include identifiable information on the surveys if they wish to complete the surveys at two time points. Upon completion of the first survey, participants will receive a study enrolment number which will be documented on all study documents and pre-populated on their second survey to enable the research team to link their results.

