**Study 2**

Study 2 participants are consenting to (1) participate in a telephone interview to provide feedback on the campaign. At time of follow-up assessment, participants will be contacted and provided with an opportunity to provide their opinion on the Brain Bootcamp campaign. They will be asked to provide consent to participate in a telephone interview that will be recorded and transcribed. We will attempt to reach out to individuals who dropped out of the study (i.e. those who did not update their brain health profile at three-month follow-up).

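### Study 1's primary paired t test describes only those who return the three-month survey, although a quarter are expected not to; the direction and size of any bias are unknown

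*Protocol*

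**What the plan says.** Protocol section 8.2 (Study 1) names both the test and the outcome: "Paired sample t tests will be used to analyse changes in our primary outcome", which it gives as the risk profile, compared between baseline and month three. The Analysis plan in the Summary says that "paired sample t-tests will be conducted to examine and analyse changes in primary outcome", and there it covers dementia awareness as well as the risk profile.

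Section 8.1 (Study 1) allows for "a drop out rate of 25" per cent. Section 6.5 (Study 2) explains drop-outs as "those who did not update their brain health profile at three-month follow-up", so every drop-out lacks the primary endpoint. Section 6.4 (Study 1) makes linkage to the second survey voluntary: identifiers are requested from people "if they wish to complete the surveys at two time points".

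The only step on missing data in section 8.2 is this: "All surveys will be visually inspected for completeness on collection to minimise missing data". That concerns surveys that arrive and does nothing about surveys that do not. Sections 6.2, 6.5 and 8.1 plan interviews with a sample of drop-outs to learn why they stopped, but that work is qualitative and does not feed into the estimate of change.

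**The concern.** A paired t test has no contribution from a person with one score. Run as written, it estimates change among responders, whereas hypothesis 1 in section 2 is about older adults who receive the campaign.

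Responders select themselves, and in a lifestyle campaign the decision to return may well be related to how much a person changed. Study 1 is a single-group pre-post study, so there is no comparison arm in which similar losses could partly cancel. Whatever difference exists between returners and non-returners goes straight into the headline change.

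The baseline risk profile, motivation, PHQ-9 and demographics of those who leave are collected before the box is sent, and the named primary test does not use them. What is at stake is the size of the reported change and the population to which it applies.

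**Working it through.** **Inputs from the protocol.** Planned N = 500 (Summary; section 4.2). Drop-out 25% (section 8.1). Assumed change of minus "0.3 Z score, SD = 0.5" (section 8.1). I take 0.5 as the SD of the change, which the protocol does not state.

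**The plan's own figure.** Section 8.1 gives 403 as the required sample. It does not follow from the stated inputs: ((1.960 + 1.282) × 0.5 / 0.3)² gives 30, and 30 / 0.75 = 40 (32 and 43 with the t distribution). That is a separate matter and does not affect this point. I use 500 below and show 403 where it matters.

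**Who is analysed.** 500 × 0.75 = 375 completers, so 125 people do not contribute. With 403 enrolled, 403 × 0.75 ≈ 302, so about 101 do not.

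**A. If drop-outs change by a different amount.** Let completers change by -0.30 and drop-outs by m. The change over all enrolled is 0.75 × (-0.30) + 0.25 × m.

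| Assumed m | All enrolled | Completer figure larger by |
|---|---|---|
| -0.30 (same) | -0.300 | 0% |
| -0.15 (half) | -0.2625 | 14% |
| 0 (none) | -0.225 | 33% |
| +0.30 (equal worsening) | -0.150 | 100% |

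The third row can equally be read as the all-enrolled value being 25% smaller than the completer value. For the all-enrolled change to be zero, m would have to be 0.75 × 0.30 / 0.25 = +0.90.

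**B. If return depends on a measured baseline variable, such as motivation.** Here -0.30 is the true mean over all enrolled. Let X be the standardised baseline variable. The log-odds of return are linear in X, with the intercept set so that 75% return, and X has correlation r with improvement. Then

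completer mean = -0.30 - r × 0.5 × E(X | returned).

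E(X | returned) is 0.098, 0.160 and 0.228 for odds ratios of 1.5, 2 and 3 per SD. The odds ratios and correlations are assumptions; the protocol gives none.

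| Odds ratio per SD | r = 0.1 | r = 0.2 | r = 0.3 | r = 0.4 |
|---|---|---|---|---|
| 1.5 | -0.305 (1.6%) | -0.310 (3.3%) | -0.315 (4.9%) | -0.320 (6.6%) |
| 2 | -0.308 (2.7%) | -0.316 (5.3%) | -0.324 (8.0%) | -0.332 (10.6%) |
| 3 | -0.311 (3.8%) | -0.323 (7.6%) | -0.334 (11.4%) | -0.346 (15.2%) |

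With r = 0 or an odds ratio of 1, the bias is zero. If r has the opposite sign, the completer mean is too small by the same amounts.

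**C. Would the conclusion change?** Completers only: t = 0.30 / (0.5 / √375) ≈ 11.6. With zero change given to all 125 drop-outs, the mean is -0.225 and the variance is 0.75 × (0.25 + 0.09) - 0.225² = 0.204. The SD is therefore 0.452, and t = 0.225 / (0.452 / √500) ≈ 11.1. On the protocol's own figures, the sign and significance survive.

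**The case against.** The strongest reply is that this is a gap and not a misstatement. Section 8.2 names a test. It does not say completers only, and it does not rule out imputation or sensitivity analyses. A paired t test can be run on imputed data, and the handling of unreturned surveys is commonly left to a statistical analysis plan, which may exist. This stands in part: the absence of a sensitivity analysis is not an error in itself. But the section headed as the detailed plan commits to a primary method that, run as written, excludes a quarter of participants. A later document could add analyses around it, yet the named primary estimate would stay a responder estimate unless this text changes.

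Three stronger readings are tempting, and the documents do not support them.

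- *The change is likely overstated.* No section says how drop-outs differ from completers. People with poor baseline profiles could have more room to improve and also be more likely to leave, which would bias the estimate the other way.
- *Baseline data can remove the bias.* That is true only as far as baseline variables explain it. Non-use of the box happens after baseline and is not observed in people who do not return, so imputation from baseline cannot in general correct for it.
- *The campaign's apparent benefit could be an artefact of drop-out.* On the protocol's figures, drop-outs would have to worsen by 0.90 Z to cancel it.

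It is also fair to say that the protocol does not ignore attrition: the sample size allows for it, and Study 2 seeks out drop-outs. Neither corrects the estimate.

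**Conclusion.** The point holds as one about the size and population of the headline estimate. The primary analysis, as fixed, describes the roughly three quarters who choose to return, in a design where differential loss has nothing to offset it.

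The direction and size of the bias cannot be known from the documents. It is zero if loss is unrelated to change. It is about 2 to 15% under the assumed odds ratios of 1.5 to 3 per SD and correlations of 0.1 to 0.4. The completer figure is 33% larger than the all-enrolled value if drop-outs do not change. These figures take 0.5 as the SD of the change and the 25% drop-out as planned. The finding of an improvement would very probably stand, so this is a change that should be made and not a threat to the study's conclusion.

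**What to change.** In section 8.2 and in the Summary's Analysis plan:

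1. Define the primary estimate as the mean change over all participants with a baseline survey. Obtain it by multiple imputation of the three-month score, or an equivalent likelihood-based model, with baseline score, MCLHB-DRR, PHQ-9, age, gender and education as predictors.
2. Keep the completer paired t test as a sensitivity analysis.
3. Add a bound that gives drop-outs zero change. It is needed because imputation removes only the bias that the baseline variables explain.
4. Treat dementia awareness in the same way, since the Summary applies the paired t test to it too.

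The cost is plan wording and a few lines of code; no new data or contacts are needed. The downside is reliance on a missing-at-random assumption, which the zero-change bound makes visible, and a headline change that may be slightly smaller.
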